	**Daily sodium bicarbonate (Nephrotrans® 840 mg) dosage**	
**(A) Baseline treatment algorithm**	Investigational group	Control group
Mean HCO_3_^-^ of two measurements		
<18 mmol/L	5,040 mg (2 capsules TID)	2,520 mg (1 capsule TID)
18 to 19 mmol/L	4,200 mg (2 capsules BID, 1 capsule QD)	1,680 mg (1 capsule BID)
19.1 to 20.0 mmol/L	2,520 mg (1 capsule TID)	Monitor
>20 mmol/L	1,680 mg (1 capsule BID)	
**(B) Follow-up visit treatment algorithm**	Investigational group and control group	
Difference to target HCO_3_^-^ level		
−1 mmol/L	Add 1,680 mg to the previous daily dosage (+1 capsule BID)	
−2 mmol/L	Add 3,360 mg to the previous daily dosage (+2 capsules BID)	
≤ −3 mmol/L	Add 5,040 mg to the previous daily dosage (+2 capsules TID)	
+1 mmol/L	Subduct 1,680 mg from the previous daily dosage (−2 capsules)	
+2 mmol/L	Subduct 3,360 mg from the previous daily dosage (−4 capsules)	
≥ +3 mmol/L	Subduct 5,040 mg from the previous daily dosage (−6 capsules)	

QD, every day; BID, twice daily; TID, trice daily.

### Outcome parameters

The primary outcome is renal function and will be measured by means of eGFR, calculated according to the 4-variable-MDRD Study equation [36].

Secondary outcomes are death, and the need for renal replacement therapy (RRT) (patients with renal transplantation, hemodialysis, peritoneal dialysis, and subjects who are in need of RRT, but personally elect not to start it). The need for RRT will be clinically evaluated, including monitoring of uremic symptoms (nausea and/or vomiting, fatigue, deterioration in nutritional status and significant weight loss, neuropathy, encephalopathy, or psychic disturbances), blood and fluid disturbances (volume overload, malignant hypertension, anemia, bleeding diathesis, pleuritis and/or pericarditis), and significant electrolyte imbalances. A further secondary outcome is the percent change in markers of bone metabolism (bone alkaline phosphatase, osteocalcin, c-telopeptide pyridinoline crosslinks of type I collagen, and procollagen type I N-propeptide) across groups.

### Sample size

Assuming equal baseline levels of eGFR between the two study groups, a clinically relevant difference of 5 ml in eGFR after 2 years, and an estimated standard deviation of 12 ml for the change in eGFR after 2 years (pilot data, Figure 2), an independent sample *t*-test with a sample size of 2 × 100 patients will give 80% power to reach statistical significance at a two-sided significance level of 5%.

**Figure 2 F2:**
[figure not shown]
**Cohort analyzed to calculate the sample size.** CKD, chronic kidney disease; eGFR, estimated glomerular filtration rate.

### Statistical methods

The intention-to-treat population will be used for statistical analysis. The primary analysis focuses on the estimated treatment effect at 2 years (difference between the two groups in eGFR after two years), which will be provided as the point estimate at the expected difference, 95% confidence interval and *P*-value. Mortality of patients or other reasons for dropout will be addressed by jointly modeling longitudinal eGFR and time to death using an appropriate joint model for longitudinal and time-to-event outcome [37]. In the longitudinal part of this model, a linear mixed model will be used with the repeated eGFR measurements as outcome values, and including as fixed factors treatment group, all stratification criteria (age, diabetes, severity of acidosis, previous alkali treatment), the eGFR baseline value and time since start of treatment, and a random intercept. An interaction effect (product term) of the treatment group and the time since start of treatment will also be included. Graphical diagnostic tools (residual plots) will be used to confirm the adequacy of model assumptions. A secondary outcome is time to death, compared between the treatment groups, which will also be estimated by the joint modeling approach. The time up to the point of need of RRT will be compared between the two treatment groups, accounting for death as a competing risk, by modeling the cumulative incidence function [38], including treatment group and the covariates age, diabetes, severity of acidosis and baseline eGFR. Percent change (from baseline to week 20 and baseline to week 104, respectively) in markers of bone metabolism will be analyzed by analysis of covariance, to adjust for sex, age, change in renal function, and baseline values of the bone markers. The incidence of serious adverse events will be reported and compared between groups using the chi-squared test. Baseline parameters (etiology of CKD, relevant medical disease, age, gender, concomitant medication, blood pressure, number of antihypertensive medications, and laboratory measurements) will be analyzed descriptively for the interventional and control group, respectively. SAS (Version 9.3, SAS Institute Inc., Cary, NC, USA, 2011) will be used for data management and analysis, and R 2.12.2/package JM [37] will be used for the main outcome analysis.

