### Randomization and study visits

Subjects will attend the clinic for a regular visit and blood draw. After a careful review of their medical history patients who fulfill the inclusion criteria will be contacted and informed about the study protocol. Patients who agree to participate in the study will be invited to a further blood work-up to ensure that metabolic acidosis is chronic rather than a one-time imbalance of the acid–base status. After obtaining written informed consent (day 0) each patient will be randomized 1:1 either to the treatment group or the control group (Figure 1). Subjects will be stratified for age >60 years and ≤60 years [34], presence of diabetes mellitus (yes/no) [35], severe chronic metabolic acidosis (serum HCO_3_^-^ <18 mmol/L) versus moderate metabolic acidosis (serum HCO_3_^-^ ≥18 mmol/L), and for previous alkali treatment (yes/no). Previous alkali treatment is defined as being continued for longer than 6 months (>25% of the treatment period of the planned study) and serum HCO_3_^-^ ≥20 mmol/L on more than 75% of measurements. Stratified randomization will be carried out using the web-based randomizer program provided by the Medical University of Vienna [https://www.meduniwien.ac.at/randomizer/web/login.php]. We use the minimization method with a preferred treatment probability of 0.9, and a combination depth of 2.0, to guarantee that treatment allocation is balanced in all levels of the stratification factors, as well as in all pairwise combinations of stratification factors. After randomization, subjects will receive either the high dose of sodium bicarbonate or, if necessary, a low-dose rescue therapy with sodium bicarbonate.

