## Discussion

In 1931 Lyon *et al.* described for the first time the simple approach of compensating metabolic acid excess in a series of 17 patients with chronic nephritis by providing an alkaline diet or substituting alkaline salts [39]. In 2012 the question of whether or not systematic treatment of metabolic acidosis in CKD is indicated is still to be addressed by the scientific community, due to the paucity of acceptable evidence [40-42].

Indeed, patients with CKD comprise a difficult study cohort in terms of sample size calculation and accurate methodological planning, due to severe comorbidities and increased mortality [25,43-47]. De Brito-Ashurst *et al.*[28] tried to show that correcting metabolic acidosis stabilizes renal function in patients with CKD stage IV. In the open-label study the control group had a significantly greater decline in creatinine clearance (5.93 mL/min) compared to the treatment group (1.88 mL/min) after 2 years. Furthermore, subjects in the treatment group presented with significantly slower progression of CKD (defined as creatinine clearance loss >3 mL/min/year) (9% versus 45% in the control group). However, critical issues concerning the study methodology are that first, rapid progression and development of ESRD are competing endpoints, and second, the way this was handled in the data analysis is unclear. They stated that ‘the rate of decline of creatinine clearance was similar between the two groups up to 12 months of follow-up because of dropout of 17 patients of the control group who had rapid decline and reached ESRD between 6 and 12 months’. However, only 15 dropouts are depicted in the respective Kaplan-Meier curve (Figure three in de Brito-Ashurst *et al.*[28]) between months 6 and 12. This might be the source of confounding and can be avoided by using a more appropriate competing endpoint analysis [48]. Further, the need of that additional endpoint is questionable, because subjects with rapid decline in renal function essentially reach ESRD at some point in time. Also, the control group was treated with ‘standard care’ with no further explanation whether that protocol included sodium bicarbonate supplementation. If this was not the case, the administration of placebo in the control group might have been indicated.

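### The joint model for the primary outcome has death as its only event, so it does not address exit at renal replacement therapy as promised, and the 2-year eGFR difference can be pulled towards zero

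*Protocol article*

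**What the plan says.** All references are to the protocol article.

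- **Statistical methods, primary analysis.** The target is the between-group eGFR difference at 2 years in the intention-to-treat population. On incomplete follow-up: "Mortality of patients or other reasons for dropout will be addressed by jointly modeling longitudinal eGFR and time to death". The longitudinal part is a linear mixed model on the repeated eGFR values with treatment, stratification factors, baseline eGFR, time, treatment by time, and a random intercept. No random slope is named.
- **Statistical methods, secondary analyses.** The time-to-death comparison is taken from the same joint model, so the event there is death and not a composite. RRT has its own cumulative-incidence analysis with death as competing risk. That analysis is not linked to the eGFR trajectory.
- **Outcome parameters.** "Secondary outcomes are death, and the need for renal replacement therapy (RRT"). The need for RRT is judged clinically and includes patients who need it but choose not to start.
- **Randomization and study visits, Table 1.** Laboratory tests run at every visit to week 104, with no different schedule after RRT.
- **Discussion.** The earlier bicarbonate trial in stage IV disease is criticised because "rapid progression and development of ESRD are competing endpoints" and their handling was unclear.

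**The concern.** A survival submodel for death links the eGFR trajectory to death and to nothing else. Every other exit is censoring, and the model learns nothing from it. The sentence on dropout therefore promises more than its method can give.

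RRT is the exit that matters most. Patients enter with eGFR between 15 and 60, and the fastest decliners are the ones who start dialysis or receive a transplant. If bicarbonate works, more of them are in the control arm. Two things can then happen to the primary estimate:

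1. **The series ends at RRT.** With a random intercept only, all patients in an arm share one slope. The steep part of the leavers' decline is lost, and the control arm looks better than it was.
2. **The series continues after RRT.** Dialysis removes creatinine and a transplant restores filtration, so the MDRD value no longer measures the patient's own kidneys. Transplant values in particular raise the control mean.

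Both work against a true benefit. What is at stake is the size of the primary effect and the power to detect it.

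**Working it through.** **1. The plan's own figure.** Inputs from Sample size: "a clinically relevant difference of 5 ml in eGFR after 2 years", "an estimated standard deviation of 12 ml for the change in eGFR after 2 years", "with a sample size of 2 × 100 patients will give 80% power to reach statistical significance" "at a two-sided significance level of 5"%. Allocation, from Randomization and study visits: "each patient will be randomized 1:1 either to the treatment group or the control group".

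Standard error = 12 × √(2/100) = 1.697. Noncentrality = 5 / 1.697 = 2.946. The noncentral t distribution with 198 degrees of freedom gives power 83.4%; 80% needs 92 per arm. The stated 80% is thus slightly conservative. This is not part of the present point and serves only as a reference.

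**2. Which exits are modelled.**

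| Exit from the eGFR series | In the joint model? | Elsewhere? |
|---|---|---|
| Death | Yes, as the event | Time to death, same model |
| Dialysis or transplantation | No, censoring | Separate competing-risk analysis |
| Other dropout | No, censoring | No |

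The promise covers all three rows; the model covers the first.

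**3. Size, by simulation.** Taken from the document: the visit weeks, baseline eGFR 15 to 60, a 2-year difference of 5 and SD of change 12. Assumed, because the document does not give them: mean baseline eGFR 28 or 35, control slope −4 per year, measurement SD 3, an alternative SD of change of 8, and RRT once eGFR falls below 8, 10 or 12, judged on either the measured or the latent (error-free) value.

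Latent eGFR = baseline + slope × years. Mean slope is −4 in controls and −4 + 5/2 = −1.5 in treated patients. Slope variance = (SD of change² − 2 × 3²)/4, which is (144 − 18)/4 = 31.5 for SD 12 and (64 − 18)/4 = 11.5 for SD 8.

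Each scenario had 8,000 patients, fitted by maximum likelihood with treatment, baseline eGFR, time and treatment by time. The estimate is the treatment coefficient + 2 × the interaction. Stratification factors and deaths were not simulated, so the longitudinal part stands in for a death-only joint model. Each shift is the estimate minus the fit to the same data without RRT.

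Four of the 24 scenarios:

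| Mean baseline; SD of change; RRT rule | RRT control / treated | No RRT | Stopped at RRT, random intercept | Stopped at RRT, random slope | Dialysis-level values kept, random intercept | 30% of RRT transplanted, values kept, random intercept |
|---|---|---|---|---|---|---|
| 35; 8; measured <8 | 6% / 2% | 4.91 | 4.85 | 4.92 | 4.87 | 4.68 |
| 28; 12; measured <10 | 23% / 14% | 4.90 | 4.40 | 4.94 | 4.53 | 3.67 |
| 28; 12; latent <10 | 21% / 11% | 4.96 | 4.16 | 4.76 | 4.54 | 3.52 |
| 28; 12; latent <12 | 24% / 14% | 4.67 | 3.95 | 4.44 | 4.38 | 3.21 |

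Dialysis values were set near 8 and transplant values near 50. Over all 24 scenarios (RRT in 4–29% of controls and 1–20% of treated patients) the shifts were:

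- stopped at RRT, random intercept: −0.06 to −0.52 (measured rule), −0.14 to −0.80 (latent rule);
- stopped at RRT, random slope: −0.01 to +0.06 (measured), −0.04 to −0.23 (latent);
- dialysis-level values kept, random intercept: −0.01 to −0.45;
- 30% of RRT patients transplanted and their values kept, random intercept: −0.21 to −1.46.

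A further simulation (mean baseline 30, SD 12, RRT in about 17–24% of controls) agreed. Stopping at RRT under a random intercept cost about 0.1–0.45 mL, and a random slope removed nearly all of it. Keeping post-RRT values with 25% transplanted cost 0.6–0.9 mL with or without a random slope.

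**4. Confidence-interval coverage.** Trials of 100 per arm, SD 12, mean baseline 30, 200 trials per cell:

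- random intercept, no RRT: mean 5.1, coverage 70%;
- random intercept, stopped at latent eGFR below 10 (RRT 20% versus 12%): mean 4.4, coverage 69%;
- random slope, same dropout: mean 5.0, coverage 96%.

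The low coverage is there without any RRT.

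**5. What the shift means for power.** In the reference t-test, a difference of 5 − 0.80 = 4.20 gives 69% power, and 5 − 1.46 = 3.54 gives 55%, against 83.4% at 5. This is only a yardstick, because the primary analysis is not a t-test.

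**The case against.** - **The 2-year difference is not shown to be biased.** A reader might infer that a death-only event must bias it. RRT that follows recorded eGFR is missing at random, and with a random slope the simulated bias was then essentially zero. This stands, so the claim is that bias can arise. Missingness at random cannot be taken for granted, however: the need for RRT is judged on symptoms, volume and electrolytes in an open-label trial.
- **The article does not say that post-RRT values will be used.** The intention-to-treat sentence defines the population, not which measurements count, and a condensed article may leave that cut-off to the full plan. This stands too. The transplant scenario is conditional, and the silence alone would not be a finding. The naming of death as the sole event is a positive statement and does not depend on that silence.
- **Poor coverage should not be blamed on RRT.** It comes mainly from the missing random slope, as step 4 shows.
- **RRT is not ignored.** The Discussion calls for a competing-endpoint analysis, and the plan adopts one for the secondary RRT outcome. That is fair. It leaves the primary eGFR model untouched.
- **Keeping dialysis-level values is partly a different question**, the effect whatever treatment follows, and not purely bias. True, but the plan would need to state that choice.

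**Conclusion.** The point holds in this form: the dropout sentence claims a handling of non-death exits that a model for time to death cannot supply, and RRT is the exit most closely tied to eGFR. With a random intercept only, this can pull a true 5 mL difference towards zero by roughly 0.1–0.8 mL if the series ends at RRT. If values after transplantation are kept, the loss is roughly 0.2–1.5 mL. Every random-intercept scenario moved in that direction, and all assumed a real benefit.

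The sizes depend on baseline, slope, RRT and transplant assumptions that the document does not supply. They are small where RRT is rare. Certain bias, actual use of post-RRT values, and undercoverage caused by RRT are stronger readings that the document does not support. Severity: should be fixed before outcome data are seen.

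**What to change.** 1. State that eGFR counts in the primary model only up to the start of RRT, and continue follow-up for death afterwards.
2. Include RRT as a terminal event beside death, preferably as two cause-specific hazards each linked to the eGFR trajectory. A composite event would be simpler, but the planned time-to-death comparison comes from this model and would then need a separate analysis.
3. Add a random slope for time. Adding RRT as an event without it need not cure the shift. Conversely, a slope alone does not help if post-RRT values are kept.
4. Say whether patients who need RRT but decline it have the event, since their eGFR remains native.
5. Add a sensitivity analysis for the handling of eGFR at and after RRT.

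The random slope with the series stopped at RRT was simulated; the cause-specific joint model was not, so its gain is argued and not measured. The cost is analysis text and a slightly more complex model. RRT and death are already secondary outcomes analysed as times to event, so no new data are needed.

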## Background

Chronic kidney disease (CKD) occurs in approximately one in ten persons worldwide and represents not only a medical challenge but also a great socioeconomic burden. Major efforts have been made to investigate treatment options aiming to slow progression to end-stage renal disease (ESRD) and, subsequently, to reduce mortality in kidney patients. A renin-angiotensin system blockade with either angiotensin-I-converting enzyme inhibitors or angiotensin-II-receptor antagonists slows the progression of decline in renal function [1-5]. However, further therapeutic interventions have not shown any benefits [6-10]. The comprehensive summery by Fink *et al.* underscores the lack of evidence-based treatment concepts in CKD and even calls screening and monitoring for early-stage CKD into question [11].

Overt chronic metabolic acidosis in CKD patients develops after a drop in glomerular filtration rate (GFR) to less than approximately 25 mL/min/1.73 m^2^. The pathogenic mechanism seems to be a lack of tubular bicarbonate production, which in healthy individuals neutralizes the acid net production. As shown in several animal and human studies the acidotic milieu alters bone and vitamin D metabolism [12], induces muscle wasting [13], and impairs albumin synthesis [14], in addition to other detrimental effects [15,16]. Experiments in rats suggest that even in the earlier stages of CKD with serum bicarbonate levels within normal limits, increased per-nephron acidification occurs to obviate overt metabolic acidosis [17]. Investigations to elucidate the contribution to the progression of CKD itself have provided contradictory results [18-20]. However, there is evidence that the alternative complement system is activated by increased tubular ammonia production [21] and that endothelin, angiotensin II and aldosteron kidney concentrations are increased as a direct result of distal nephron acidification [17,20,22]. Taken together, these alterations induce tubulointerstitial scarring in the long term.

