**Figure 1 F1:**
[figure not shown]
**Study design. **^*^Two consecutive measurements at least 1 day apart. CKD, chronic kidney disease.

Each study visit consists of a fasting blood draw (last food intake including the study medication should be at least 8 hours before) and urinalysis, measurement of vital signs, and assessment of changes in concomitant medication and adverse events (Table 1). At the beginning of the study a physical examination will be done and body weight and height will be assessed. Study visits will be performed at weeks 4, 8, 12, 20, 29, 38, 47, 60, 73, 86, and 104.

**Table 1 T1:** Visit and assessment schedule

	**Screening period (4 weeks)**							**Treatment period (0 to 24 months)**					
		**Day 0**	**Week 4**	**Week 8**	**Week 12**	**Week 20**	**Week 29**	**Week 38**	**Week 47**	**Week 60**	**Week 73**	**Week 86**	**Week 104**
			**(± 2 days)**	**(± 2 days)**	**(± 2 days)**	**(± 5 days)**	**(± 5 days)**	**(± 5 days)**	**(± 5 days)**	**(± 10 days)**	**(± 10 days)**	**(± 10 days)**	**(± 10 days)**
**Visit**	1	2	3	4	5	6	7	8	9	10	11	12	13
**Informed consent**		x											
**Inclusion/exclusion criteria**	x	x											
**Randomization**		x											
**Medical history**		x											x
**Concomitant medication**		x	x	x	x	x	x	x	x	x	x	x	x
**Physical examination**		x											x
**Body weight and height**		x											x
**Vital signs (BP, PR)**		x	x	x	x	x	x	x	x	x	x	x	x
**Laboratory test**	x	x	x	x	x	x	x	x	x	x	x	x	x
**Laboratory test: bone markers**		x				x							x
**Biobank sample**		x				x			x		x		x
**Urinalysis**	x	x	x	x	x	x	x	x	x	x	x	x	x
**24-hour urine collection**	x^a^	x^a^	x			x			x				x
**Urine pregnancy test**^**b**^		x	x	x	x	x	x	x	x	x	x	x	x
**Adverse events**			x	x	x	x	x	x	x	x	x	x	

^**a**^To be performed either at screening visit 1 or screening visit 2. prior to randomization; ^**b**^for females of childbearing age only. BP, blood pressure; PR, pulse rate.

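### The primary model may leave precision unused: acidosis enters as a two-level factor, and baseline RAS-blocker use is only described

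*Protocol article*

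**What the plan says.** The primary analysis in Statistical methods targets the "difference between the two groups in eGFR after two years". It uses a joint model whose longitudinal part is a linear mixed model "including as fixed factors treatment group, all stratification criteria (age, diabetes, severity of acidosis, previous alkali treatment), the eGFR baseline value". The model also has a time effect, a random intercept for each patient and a treatment-by-time product term. No covariate-by-time term is listed.

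Randomization and study visits defines the criteria used in the minimisation: age above versus up to 60 years, diabetes, bicarbonate below 18 versus 18 mmol/L or above, and previous alkali treatment.

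More baseline information than this is collected:
- Two qualifying bicarbonate values are required for entry, and Table 2A already uses their mean.
- Table 1 schedules concomitant medication at day 0, urinalysis at screening and day 0, and a 24-hour urine "To be performed either at screening visit 1 or screening visit 2. prior to randomization".

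In Statistical methods these data serve only the baseline table: "concomitant medication, blood pressure, number of antihypertensive medications, and laboratory measurements) will be analyzed descriptively". The Background states that "A renin-angiotensin system blockade with either angiotensin-I-converting enzyme inhibitors or angiotensin-II-receptor antagonists slows the progression of decline in renal function".

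**The concern.** The outcome is eGFR at 2 years, and the Background credits RAS blockade with slowing its decline. Yet RAS-blocker use is neither a minimisation factor nor a model covariate. Bicarbonate is known exactly for every patient, but the model takes it as a two-level criterion, which discards information within each level.

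Outcome variation that these values could explain stays in the error term, so the confidence interval for the 2-year difference may be wider than it need be. The Sample size section states no dropout allowance, so a modest gain could matter if fewer than 100 patients per arm are evaluable. The trial is open-label, so a covariate set chosen after the data are seen would be less credible than one fixed in advance.

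**Working it through.** **Inputs from the document (Sample size).** "a clinically relevant difference of 5 ml in eGFR after 2 years"; "an estimated standard deviation of 12 ml for the change in eGFR after 2 years"; 100 patients per arm; two-sided 5% level; t-test; stated power 80%.

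**Step 1. The plan's own figure.** SE = 12 × √(2/100) = 1.70 mL, so the 95% half-width is 1.96 × 1.70 = 3.33 mL. Exact noncentral-t power at 100 per arm is 83.4% (normal approximation 83.8%), and 92 per arm would give 80%. The stated 80% is therefore conservative for its inputs. An unstated dropout of about 8% would reconcile them (92/0.92 = 100). This neither supports nor weakens the point.

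**Step 2. Upper size of the gain.** The document gives no R² for the extra covariates, so a range is assumed. Residual SD = 12 × √(1 − R²), with the same power formula at 100 per arm:

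| Assumed additional R² | SE (mL) | 95% half-width (mL) | Power | SE reduction |
|---|---|---|---|---|
| 0 | 1.70 | 3.33 | 83.4% | 0 |
| 0.05 | 1.65 | 3.24 | 85.3% | 2.5% |
| 0.10 | 1.61 | 3.16 | 87.1% | 5.1% |
| 0.20 | 1.52 | 2.98 | 90.6% | 10.6% |

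The SD of 12 is for the unadjusted change, so the planned covariates may already absorb part of this.

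**Step 3. Main effects against time terms.** With complete data, the week-104 contrast is the arm difference at the mean visit time plus the slope difference carried forward to week 104. The 11 post-baseline visits average week 43.7. If a covariate acts on slope, a main effect removes only the first part. The share of the variance gain kept is 1 − (1 − 43.7/104)² = 1 − 0.58² = 0.66.

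A simulation at the protocol's visit weeks agrees (4,000 runs per R², 100 per arm, complete data, visit-level SD 4 mL assumed, covariate acting on slope only):

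| Assumed R² | SE reduction, main effect only | SE reduction, with covariate-by-time |
|---|---|---|
| 0.05 | about 2% | about 3% |
| 0.10 | about 3% | about 5% |
| 0.20 | about 7.5% | about 11% |

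Applied to the SE of 1.70 mL, main effects alone give power of about 85%, 86% and 89%.

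**Step 4. What a cut-point costs.** For a normal covariate with a linear effect, a split with proportion p below the cut keeps φ(z_p)²/[p(1 − p)] of the explained variance: 64% at p = 0.5, 49% at p = 0.2 and 34% at p = 0.1. The document does not say what proportion lies below 18 mmol/L in a population entering below 21 mmol/L.

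If bicarbonate explained 5% of the variance and 20% of patients lay below the cut (both assumed), the split would keep 0.49 × 0.05 = 0.0245. Using the exact value would change the SE by √(0.95/0.9755) = 0.987, a fall of 1.3%. At 10% explained, the factor is √(0.90/0.951) = 0.973, a fall of 2.7%. Recoding alone is thus a small gain.

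**Step 5. Fewer evaluable patients.** With 90 per arm (assumption), power is 79.4% at R² = 0 and 81.4%, 83.4% and 87.5% at 0.05, 0.10 and 0.20, by the Step 2 formula.

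**The case against.** The strongest reply is that this is a preference and not an error. The plan adjusts for the outcome's own baseline and for every minimisation factor, which is good practice. Leaving out other prognostic covariates does not bias a randomised linear comparison, and the confidence interval already allows for chance imbalance. Analysing factors as they were minimised is also accepted. All of this stands, and it limits the point to efficiency.

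A reader might infer four stronger things, none of which the document supports:

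- **Precision is certainly lost.** The Background reports a treatment effect of RAS blockade. It does not say that baseline use predicts 2-year eGFR beyond baseline eGFR and diabetes in these patients. If use is nearly universal, or follows disease severity, the added R² could be near zero. RAS-blocker use is also not named as a data item; it has to be derived from concomitant medication, which is recorded at the randomisation visit.
- **The model wrongly omits proteinuria.** Neither Laboratory measurements nor Table 1 names urinary protein or albumin as an analyte, and the article gives no prognostic figure for it. The Discussion mentions albuminuria only in describing another trial's population.
- **Age is dichotomised.** Statistical methods lists plain age among the stratification criteria. The same list holds baseline eGFR and time, which are continuous. Either reading is possible, and an analysis plan that is not shown may settle it.
- **The RRT model needs the same covariates.** No expected event count is given, so a shorter list there is not a defect.

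**Conclusion.** The point holds in a limited, conditional form. The covariate list is fixed in the article, and it uses bicarbonate (and possibly age) more coarsely than it is known. It also leaves out baseline RAS-blocker use, although the article itself says RAS blockade slows decline. The estimate remains unbiased, and at 100 per arm the plan's own inputs give more than the stated power.

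What may be lost is precision. The SE could fall by 0 to about 11% for an assumed additional R² of 0 to 0.20, taking the half-width from 3.33 mL to as little as 2.98 mL. If the covariates act on slope and enter only as main effects, the fall is at most about 7.5%. These figures rest on the assumed R², on an unadjusted SD of 12 mL and, for the simulation, on complete data. The case for acting is that the information is largely in hand and the change is cheap.

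**What to change.** In Statistical methods, before database lock:

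1. State that age and the mean of the two qualifying pre-treatment bicarbonate values enter the longitudinal submodel as continuous covariates. Keep diabetes, previous alkali treatment and baseline eGFR.
2. Add baseline RAS-blocker use (yes/no), as recorded at day 0 before treatment starts.
3. Give each of these covariates a covariate-by-time term, so that the gain reaches the 2-year contrast if they act on slope.
4. Add baseline urinary protein, also with a time term, only if it is already measured in the scheduled baseline urine.

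The cost is a few more model terms and a simple pre-stated rule for missing baseline values. No new visit or sample is needed, and the RRT model can stay as it is.
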